## **1.7 Risk/benefits**

There are no known risks to participating in the trial. We assume that participants in the intervention group will benefit from more in depth antenatal classes in small groups, however, we cannot rule out the possibility that the intervention group may experience an increase in worries about issues related to pregnancy and parenting. Participants randomised to the control group may experience some disappointment. The control group will receive standard care why we consider being randomised to the control group as ethically justifiable.

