### **3.4 Blinding**

It is not possible to blind participants or service providers. Data will be blinded by a data- manager and the investigators and statistician will therefore be blinded to participants' intervention category during data analyses. Participants' intervention category will first be revealed to outcome assessors and investigators after they have drawn conclusions about outcome effects of group X versus Y.

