### **3.8 Data collection**

Data will be collected from both parents using web-based questionnaires at: baseline (<20 weeks gestation), 37 weeks gestation, 9 weeks after expected due date, 6 months after expected due date, 1 year after expected due date. Participants will be contacted via e-mail, when due to answer a questionnaire. Two reminders will be sent via additional e-mails, the first after a week and the second after 14 days. Where possible a member of the project group will contact non-respondents by phone a week after the final e-mail reminder.

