## 7.2 Statistical methods

Reporting will follow the guidelines of the CONSORT-statement. Statistical analyses will be intention to treat as well as per protocol. The level of significance will be 0.05.

The analysis of the primary binary outcome will be done using the generalised linear mixed model with distribution = binomial, link = logit.

If the percent missing cases > 5%, the results of this analysis will be subjected to a 'worst case' and a 'best case' scenario analysis of the potential impact of missing values. Assume a beneficial effect (less use of epidural analgesia) is noted in one group (group A) as compared to the other group (group B). A worst case scenario will then be constructed where missing values in group A are imputed by a "yes" to use of epidural analgesia and missing values in group B are imputed by a "no" to use of epidural analgesia. A corresponding best case scenario will also be constructed and the result under both scenarios will be computed.

Analyses (adjusted by baseline value and protocol specified variables) of perceived stress at 37 week gestation and for each of the other two secondary outcomes of the area under the curve (AUC) from 9 weeks to one year after due date will be done.

If the percent missing cases of an outcome is >5% and p of Little's test (1) < 5%, a number of datasets with observed values and predicted unobserved values necessary to produce an efficiency > 99% will be produced using multiple imputations (SAS version 9.3 or later)(2). The primary analysis will then be that based on these data sets.

Multiplicity will be dealt with as follows: the primary outcome will be tested at the 5% level. The p values of the remaining four tests will be adjusted using Hommel's procedure (Konietschke, 2012). In all events all observed p values will be reported.

For the secondary outcome measure 'Perceived Stress Scale' it will be tested using the general linear univariate model, whether the mean values differ between the two intervention groups at time 1 (37 week gestation), time 2 (9 weeks following birth), time 3 (6 months following birth), and time 4 (12 months following birth).

For the secondary outcome measure 'Swedish Parenthood Stress Questionnaire' it will be tested using the general linear univariate model, whether the mean values differ between the two intervention groups at time 2 (9 weeks following birth), time 3 (6 months following birth), and time 4 (12 months following birth).

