For the secondary outcome measure 'Parenting Alliance Measure' it will be tested using the general linear univariate model, whether the mean values differ between the two intervention groups at time 3 (6 months following birth), and time 4 (12 months following birth).

The unadjusted analyses are the primary analyses. If possible all analyses will be repeated adjusted for the protocol specified stratification variable and the baseline value.

Three explorative subgroup analyses may be conducted in each case provided the subgroup interacts significantly with the intervention.

In addition to analyses performed for individuals, descriptive analyses reporting the interdependency within the couple as well as within the specific antenatal education group, and at the facilitator level will be performed by intraclass correlation.

Process evaluation will be conducted with a mixed methods approach using quantitative questionnaire data and qualitative interviews with participants and service providers. We will examine program fidelity, e.g. whether the protocol is followed in program delivery, and how much of the intended program the participants are receiving, as well as program reach e.g. what proportions of the intended groups are participating in the program, as these factors have an impact on the effect of an intervention(33). The incremental societal cost of the intervention will be computed and compared to the measured outcomes in a cost-effectiveness analysis. Direct health care costs and productivity cost in terms of labour market participation and short term absence will be calculated.

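### A non-significant Little's test leaves the unadjusted observed-data comparison primary for the questionnaire outcomes, although it does not show that missing data are harmless

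*Protocol*

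**What the plan says.** Section 7.2 (Statistical methods) of the protocol sets the rule. Its condition is "If the percent missing cases of an outcome is >5% and p of Little's test (1) < 5" per cent. If both parts hold, multiple imputation is carried out in SAS, and "The primary analysis will then be that based on these data sets". The protocol gives no other route to imputation. For the remaining case, section 7.2 states: "The unadjusted analyses are the primary analyses". Repeats adjusted for the stratification variable and the baseline value are to follow if possible.

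The same section has one missing-data safeguard that does not depend on Little's test. If more than 5% is missing, "the results of this analysis will be subjected to a 'worst case' and a 'best case' scenario analysis of the potential impact of missing values". It is worded for epidural use only.

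The secondary outcomes come from questionnaires. Section 3.8 states: "Data will be collected from both parents using web-based questionnaires at: baseline (<20 weeks gestation), 37 weeks gestation", with three further rounds up to one year after the due date. Participants know their allocation; section 3.4 says "It is not possible to blind participants or service providers".

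**The concern.** The null hypothesis of Little's test is that data are missing completely at random. With more than 5% missing, the rule lets that test choose the primary analysis. A non-significant result does not establish the null. Multiple imputation is valid both under that null and under the weaker assumption of missing at random, so nothing is gained by testing first.

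The test also answers a different question. It asks whether variables differ in mean between missingness patterns. The trial needs to know whether missingness shifts the difference between arms, and the two can part company in either direction. What is at stake is that an observed-data comparison of PSS, SPSQ or PAM stands as the primary result when non-response is related to stress differently in the two arms.

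**Working it through.** **Inputs from the protocol.** 878 per arm (section 7.1); PSS standard deviation 6 and planned difference 1 point (section 7.1); "The level of significance will be 0.05" (section 7.2).

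**Inputs assumed, because the protocol does not give them.** 20% missing; correlation of 0.5 between baseline and later PSS; drop-out log-odds of 0.05 per PSS point, which is 0.05 × 6 = 0.3 per SD; no true effect.

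**The protocol's own figure.** The standard error of the PSS difference is 6 × √(2/878) = 0.286. Then 1/0.286 = 3.49, and the power is Φ(3.49 − 1.96) = Φ(1.53) = 93.7%, as stated.

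**Bias of the observed-data comparison.** If drop-out in an arm depends on baseline stress, the baseline mean of those still observed shifts by about (proportion missing) × (slope per SD), in SD units. Multiplying by correlation × SD carries this to the outcome:

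- One arm only: 0.20 × 0.3 × 0.5 × 6 = 0.18 points.
- Alike in both arms: 0.18 − 0.18 = 0.
- Opposite directions by arm: 0.18 + 0.18 = 0.36 points.

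With 878 × 0.8 ≈ 702 observed per arm, the standard error is 6 × √(2/702) = 0.32. A bias of 0.18 gives a type I error of Φ(−1.96 + 0.56) + Φ(−1.96 − 0.56) ≈ 9%. A bias of 0.36 gives about 20%.

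**Error of the rule as written.** The figures above are for an analysis that never imputes. Under the rule, imputation takes over whenever the test rejects, so they are too large for it. I simulated the rule with 5,000 trials per scenario. Little's test was run on one complete baseline and one incomplete outcome, and baseline-adjusted regression stood in for imputation.

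| Drop-out depends on baseline stress | Test (pooled over arms) rejects | Observed-data bias; type I error | Rule: bias; type I error |
|---|---|---|---|
| Alike in both arms | about 100% | about 0; about 5% | about 0; about 5% |
| In one arm only | 71% | 0.18; 9% | 0.06; 6% |
| In opposite directions | about 5% | 0.37; 20% | about 0.35; 20% |

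The middle row can be checked by hand. The test misses in 29% of trials, and 0.29 × 0.18 ≈ 0.05, close to the simulated 0.06.

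The baseline-adjusted comparator had a bias of about 0 and a type I error of about 5% in every row. If the test is made within arms, the opposite-directions case is detected in more than 99% of trials, and the rule then has a bias of about 0 and a type I error of about 5%.

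**Missing not at random.** In a separate simulation (correlation 0.6, about 20% missing), drop-out in one arm depended on the part of the outcome that baseline does not explain, with slope 0.5 per SD. Little's test was non-significant in 94% of trials. The bias was 0.49 points both for observed data and for a missing-at-random estimator.

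**The case against.** The strongest reply is that the harm is small and partly covered. Much of it stands.

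- **Epidural use is hardly touched.** It comes from the hospital obstetric database and has the best-case and worst-case analysis whatever the test shows.
- **The rule corrects itself in part.** In the one-arm case the test usually rejects, and imputation then replaces the observed-data result.
- **The 20% figure is a constructed case.** It needs slopes that cancel between arms and a test pooled over arms. Section 7.2 does not say whether the test is pooled or which variables enter it.
- **An adjusted analysis is planned.** Section 7.2 lists baseline-adjusted analyses and adjusted repeats, which would reveal a baseline-driven discrepancy in PSS. They are not primary, however, and the repeats are only if possible. Table 1 lists no baseline SPSQ or PAM, so neither can be adjusted for its own baseline.
- **A 5% threshold is itself data-dependent.** True, but it limits the amount at risk. On the same inputs, 5% missing gives at most 0.05 × 0.3 × 0.5 × 6 = 0.045 points in the one-arm case. A significance test sets no such limit.

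A reader might infer that drop-out is likely to run in opposite directions, because section 1.7 says "Participants randomised to the control group may experience some disappointment". That sentence at most suggests more drop-out among controls. It says nothing about the relation of drop-out to stress, and drop-out that differs by arm but is unrelated to stress gives no bias.

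**Conclusion.** The flaw is real and its expected size is modest. A non-significant test of missingness completely at random can decide the primary analysis of PSS, SPSQ or PAM, and such a result does not show that the comparison between arms is sound. On the assumed inputs the rule adds about 0.06 PSS points of bias (6% of the planned 1-point difference) and about one percentage point of type I error when drop-out depends on baseline stress in one arm. It adds nothing when drop-out acts alike in both arms. About 0.35 points and 20% is a worst case under a pooled test, not a forecast. The missing proportion, correlation and slopes are all assumptions. The simulations concern PSS, and their size should not be carried over to SPSQ or PAM.

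Two stronger readings are tempting. One is that the protocol declares data to be missing completely at random when the test is non-significant. It does not say so and does not use the term complete-case; the observed-data analysis follows because no other handling is given for that branch. The other is that the trial's main conclusion is at risk, which the data source and safeguard for epidural use do not support.

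**What to change.** In section 7.2, delete the Little's-test condition. Whenever an outcome has more than 5% missing, make multiple imputation the primary analysis, imputing separately by arm from the vulnerability stratum, baseline PSS and the other waves of the outcome. Report the observed-data analysis as sensitivity. Add a sensitivity analysis for data missing not at random for PSS, SPSQ and PAM, because imputation under missing at random does not remove that bias.

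The cost is one changed sentence, one added sentence and slightly more analysis work. Imputation in SAS is already planned, and neither the data collected nor the sample size changes.

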**Participants:** 2350 pregnant women  $\geq 18$  years old, recruited before 20+0 weeks gestation, due to give birth at Hvidovre Hospital. Being legally able and willing to provide signed consent, and being fluent in Danish.

**Intervention:** Women are randomised to receive:

1) A research-based birth and parenting program. The intervention consists of 4 sessions in small groups that last for 2,5 hours per session at 25, 33 and 35 weeks of gestation, and a post-natal session 5 weeks after expected due date.

2) Standard care (control group). The pregnant woman and her partner are offered two antenatal lectures in an auditorium.

The allocation of participants to the intervention will be 1:1 to the intervention and the control group.

**Methods:** Data will be collected via questionnaires at baseline, 37 weeks gestation, 9 weeks post-partum, 6 months post-partum and 1 year post-partum, via the hospital obstetric database, and via the national registers. Analyses will be intention to treat as well as per protocol analyses – sensitivity analyses comparing results from the two will be conducted. Subgroup analysis will be conducted in relation to personal and demographic characteristics.

Process evaluation will be conducted using questionnaires and qualitative interviews. The incremental societal cost of the intervention will be computed and compared to the measured outcomes in a cost-effectiveness analysis with epidural use during labour as the primary outcome. Direct health care costs and productivity cost in terms of labour market participation and short term absence will be calculated.

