#### **Sample size**

Previous data from trials (28) and hospital databases (113) indicate that the proportion of women who use epidural analgesia during birth is between 23 and 41 %. The proportion is higher among first-time mothers. Assuming that the majority of included participants in the NEWBORN trial will be first-time mothers, it is plausible to assume a proportion of epidural use of 31 % in the control group. If use of epidural analgesia can be reduced from 31 % in the control group to 25 % in the experimental group (risk reduction of 16.7 %), with a type I error (alpha) of 5 % and a type II error of 20 % (power of 80), then this requires randomisation of a total of 878 women to the intervention group and 878 women to the control group.

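### Subgroup effects are to be estimated only after a significant interaction, which selects and, for small to moderate interactions, inflates them; the Abstract sets no such condition

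*Protocol*

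**What the plan says.** Section 7.2 of the Protocol limits the subgroup work in one sentence: "Three explorative subgroup analyses may be conducted in each case provided the subgroup interacts significantly with the intervention". The analyses are optional, labelled explorative, three in number for each case, and open only after a significant interaction test. No separate significance level is given for that test; the general statement in the same section is "The level of significance will be 0.05".

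The Methods paragraph of the Abstract reads differently: "Subgroup analysis will be conducted in relation to personal and demographic characteristics". It contains neither the word may nor a significance condition.

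Two further sentences in 7.2 bear on reporting: "Reporting will follow the guidelines of the CONSORT-statement", and, at the end of the multiplicity paragraph, "In all events all observed p values will be reported". That paragraph deals with the primary test and with the secondary tests ("The p values of the remaining four tests will be adjusted using Hommel's procedure"); it does not mention interaction tests.

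The sample size in section 7.1 rests on the overall comparison for epidural use: "If use of epidural analgesia can be reduced from 31 % in the control group to 25 % in the experimental group". No power is stated for any interaction.

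**The concern.** Testing the interaction is the right way to ask whether an effect differs between subgroups. The difficulty is the next step, where significance of that test becomes the entry condition for estimating the subgroup effects at all. In a trial powered for the main effect, interaction tests have low power. Estimates that exist only because the test crossed 0.05 are therefore a selected set, and on average they lie too far apart. Where the test does not cross 0.05, the reader gets no subgroup effect and no interval showing how large a difference remains compatible with the data.

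The Protocol gives reasons to care who benefits. The region plans to offer small groups to all expectant parents (section 1.8.1), uptake may depend on socioeconomic position (section 2), epidural use is higher in first-time mothers (section 7.1), and randomisation is stratified by vulnerability (section 3.2). Unselected estimates with intervals would serve that question and later pooling; gated estimates would not.

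Separately, a rule that permits an analysis on a condition and a statement that the analysis will be done cannot both be followed.

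**Working it through.** **Inputs from the Protocol.** Epidural use 31% in control and 25% in the experimental group, alpha 5%, power 80%, 878 women per arm (section 7.1). Recruitment of 2350 at 1:1, that is 2350/2 = 1175 per arm (Abstract). Significance level 0.05 (section 7.2).

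**Assumptions, not in the Protocol.** One two-level subgroup, split 50/50 unless stated; control rate 31% in both levels; interaction tested two-sided at 0.05. A 6-point interaction means effects of -9 and -3 points (intervention rates 22% and 28%). A 12-point interaction means -12 and 0 points (19% and 31%).

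**Step 1: reproduce the stated sample size.** With pooled variance, two-sided:

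n = [1.96 × √(2 × 0.28 × 0.72) + 0.842 × √(0.31 × 0.69 + 0.25 × 0.75)]² / 0.06² = (1.245 + 0.533)² / 0.0036 ≈ 878 per arm.

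This matches, so the trial has 80% power for the 6-point main effect and was not sized for anything finer.

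**Step 2: normal approximation for the interaction at 878 per arm.**
- SE of the main effect = 6 / 2.80 = 2.14 points.
- SE of the interaction = 2.14 × √(1/f + 1/(1 - f)), where f is the fraction in one subgroup. At f = 0.5 this is 2.14 × 2 = 4.28 points.
- Power for a 6-point interaction: z = 6 / 4.28 = 1.40, and Φ(1.40 - 1.96) + Φ(-1.40 - 1.96) = 28.8%.
- The mean absolute estimate among significant results is 1.85 times the truth.

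**Step 3: the same on the logit scale**, which is the link in section 7.2, with 439 women per arm in each subgroup.
- Difference in log odds between 28% and 22% = -0.944 - (-1.266) = 0.321 (from unrounded values).
- Variance = 2/(439 × 0.31 × 0.69) + 1/(439 × 0.22 × 0.78) + 1/(439 × 0.28 × 0.72) = 0.0213 + 0.0133 + 0.0113 = 0.0459, so SE = 0.214.
- z = 0.321 / 0.214 = 1.50, and power ≈ Φ(1.50 - 1.96) = 32%.

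**Step 4: simulation of what the condition lets through.** 400,000 trials per row, logit interaction test; effects are summarised as risk differences in percentage points.

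| Per arm | Split | True difference between subgroup effects | Passes | Mean absolute estimate when passed | Ratio to truth |
|---|---|---|---|---|---|
| 878 | 50/50 | 6 | 32% | 10.7 | 10.7/6 = 1.8 |
| 878 | 30/70 | 6 | 28% | 11.6 | 11.6/6 = 1.9 |
| 1175 | 50/50 | 6 | 41% | 9.5 | 9.5/6 = 1.6 |
| 878 | 50/50 | 12 | 86% | 13.1 | 13.1/12 = 1.1 |
| 878 | 50/50 | 0 | 5% | 9.9 | not defined |

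**Step 5: remove the condition.** With the 6-point interaction, 878 per arm and a 50/50 split, the mean absolute estimate over all trials is 6.3 points, against 10.7 among those that pass. The excess comes from the selection.

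**The case against.** The strongest defence is that the sentence is a safeguard. Requiring an interaction test before looking within subgroups guards against over-reading within-subgroup p values, the number is capped at three, and the analyses are called explorative. This stands as far as interpretation goes. It argues for reading subgroup effects through the interaction test, not for leaving them unestimated when that test is not significant.

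A reader might infer something stronger: that the plan is a publication filter under which non-significant subgroup results will be concealed. The Protocol does not support that. The sentence governs what is conducted, and nothing says a non-significant interaction will be withheld. The interaction has to be tested in every case for the condition to operate. Section 7.2 commits to CONSORT and to reporting observed p values, section 12.2 to publication whether findings are positive or negative, and section 9 to making an anonymised dataset available. Whether the p-value sentence reaches interaction tests is arguable, given where it stands. Even if it does, a p value is neither an effect estimate nor an interval, and that narrower gap remains.

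A reader might also add the chance of false-positive interactions over many tests. That depends on how many tests are done, and dropping the condition would not change it, so it is no part of this point.

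Lastly, a statistical analysis plan may exist. Naming the subgroups and laying out the tables belong there, and their absence here is not a fault. Removing the condition, however, would require that plan to contradict section 7.2.

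It is also fair to say that the inflation depends on the assumed interaction: it is slight when the true difference is large, and smaller at the Abstract's recruitment figure.

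**Conclusion.** The point holds in limited form. Section 7.2 and the Abstract disagree on whether subgroup analysis is conditional and must be reconciled. As section 7.2 stands, subgroup effects and their intervals would be produced only after a significant interaction, and for small to moderate interactions those estimates are inflated.

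For epidural use with two equal subgroups and a true 6-point difference in effect, about 29 to 32% of trials pass at 878 per arm with roughly 1.8-fold overestimation, and about 41% pass at 1175 per arm with roughly 1.6-fold. At 12 points and 878 per arm, 86% pass and the inflation is about 1.1-fold. These figures rest on the assumed split, a control rate of 31% in both subgroups and a two-sided 0.05 test; they were worked out for the epidural outcome only.

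The primary and secondary conclusions do not depend on these analyses. Severity is minor to moderate.

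**What to change.** In section 7.2, delete the condition that the subgroup must interact significantly. State instead that the three pre-specified explorative subgroup analyses will be reported for the primary and secondary outcomes whatever the interaction p value, each giving the interaction estimate and the effect in every subgroup with 95% confidence intervals. Label them exploratory and say that they are interpreted through the interaction test, which keeps the safeguard. Reword the Methods paragraph of the Abstract to match. Which subgroups are meant can be set in the statistical analysis plan.

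The cost is one sentence in section 7.2, one aligned sentence in the Abstract and one extra results table. The downside is that some of the published intervals will be wide and inconclusive. No change to sample size or data collection is needed.

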#### **3.3 Trial intervention**

Intervention: The intervention is developed using a systematic framework for health promotion program planners "Planning health promotion programs: an intervention mapping approach" (33). This systematic framework aids effective decision making at each step in intervention planning, implementation, and evaluation (33).

The intervention consists of a research-based general birth and parenting training program. The intervention will have two arms:

- 1) A research-based parenting program based on the recommendations from the National Board of Health and inspired by "Towards Parenthood" (35) and "Prevention and Relationship Enhancement Program" (PREP). The intervention arm is described in more detail below.

2) Standard care (control group). The pregnant woman and her partner are offered two antenatal lectures in an auditorium.

The intervention arm: Groups of approximately 6-7 couples (or mothers) will meet three times during pregnancy and 1 time 5 weeks after expected due date, for the duration of 2.5 hours per session. (The aim is to create groups of 6-7 couples; however, due to fluctuations in uptake groups of 4-9 couples will be deemed acceptable). The sessions will include information and discussions about emotions and expectations related to birth and parenting, identification of social network resources, couple communication, breastfeeding, parent-child attachment, directions on taking care of a newborn, and recognising common signs of mood disorders and how to react. A patient-network website which enables parents to gain further information, communicate with other parents and consult online with a midwife and a health visitor will be created. In addition to gaining knowledge about issues related to birth and parenting, and creating an environment where parents can discuss their feelings and concerns, the program aims at enhancing expectant parents' awareness of their own resources and problem-solving strategies. Furthermore the way the groups are composited will enable participants to establish relations with other expectant parents in their local area. All sessions will be led by a midwife. The postnatal session will be conducted in collaboration with a health visitor, to increase knowledge on available resources in the local communities

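### Small-group teaching in the intervention arm creates clustering that the secondary tests omit, the primary mixed model leaves unspecified, and the 878 per arm does not allow for

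*Protocol*

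**What the plan says.** Section 3.1 describes an individually randomised trial. Under section 3.3, intervention women are taught together: "Groups of approximately 6-7 couples (or mothers) will meet three times during pregnancy", with 4-9 couples acceptable, a further session after birth, and a midwife leading every session. Control women are offered two auditorium lectures. Clustering by teaching group therefore arises in one arm only.

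Section 7.2 gives the primary outcome, epidural use, a generalised linear mixed model with binomial distribution and logit link, and names no random effect. For the Perceived Stress Scale (PSS), the Swedish Parenthood Stress Questionnaire (SPSQ) and the Parenting Alliance Measure (PAM), the wording each time is that "it will be tested using the general linear univariate model". The unadjusted analyses are primary, and the adjusted repeats add only the stratification variable and the baseline value. Dependence is addressed in one sentence, through an intraclass correlation and as a supplement to the individual-level analyses: "descriptive analyses reporting the interdependency within the couple as well as within the specific antenatal education group, and at the facilitator level will be performed".

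In section 7.1, "it is plausible to assume a proportion of epidural use of 31 % in the control group", the intervention rate is taken as 25%, and "this requires randomisation of a total of 878 women to the intervention group and 878 women to the control group". No ICC or design effect appears. The Abstract gives 2350 participants.

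**The concern.** The programme is meant to work through what group members share. Section 5 describes group discussion, learning from one another, feedback and a facilitating midwife, and treats the group as a possible support network. If some groups or midwives do better than others, outcomes within a group are correlated, and the mean of the intervention arm varies more than an independent-observations formula allows.

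A test that ignores this has a standard error that is too small, an interval that is too narrow and an error rate above 5%. The Hommel adjustment planned for the secondary tests cannot repair this, because it takes the p values as valid. A sample size without a design effect also overstates power. The protocol names the right sources of dependence (couple, group, facilitator) but ties none of them to a test.

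**Working it through.** **Inputs.** Epidural rates of 31% and 25%, alpha 5% and power 80% (section 7.1); the two-sided form reproduces the stated size. Group size 6.5, the middle of 6-7 (section 3.3). Sizes of 878 per arm (section 7.1) and 2350 / 2 = 1175 per arm (Abstract, 1:1 allocation). The ICC is not given; 0.02, 0.05 and 0.10 are assumptions.

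**Step 1: reproduce the plan's figures.** With pooled rate 0.28 under the null:

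n = [1.96 × √(2 × 0.28 × 0.72) + 0.8416 × √(0.31 × 0.69 + 0.25 × 0.75)]² / 0.06² = 3.1604 / 0.0036 = 877.9, so 878 per arm.

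This is the stated number with no continuity correction and no design effect. The secondary figures also reproduce under independence, from power = Φ(d / (SD × √(2/878)) − 1.96): PSS 93.7%, SPSQ 98.7%, PAM 98.7%.

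**Step 2: design effect in the intervention arm only.** DE = 1 + (6.5 − 1) × ICC. The control arm stays at 1.

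**Step 3: true error of a test that ignores clustering.** With equal arms and equal outcome variance under the null, the true standard error is √((1 + DE)/2) times the naive one, so the error is 2 × [1 − Φ(1.96 / √((1 + DE)/2))]. For ICC 0.05: DE = 1.275, ratio = √1.1375 = 1.067, 1.96 / 1.067 = 1.838, error 6.6%. The sample size does not enter the formula.

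**Step 4: primary power with a correct standard error.** SE0 = √(0.28 × 0.72 × (1 + DE)/n), SE1 = √((0.2139 + 0.1875 × DE)/n), and power = Φ((0.06 − 1.96 × SE0) / SE1). For ICC 0.05 and n = 878: SE0 = 0.02286, SE1 = 0.02271, power = Φ(0.669) = 74.8%.

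| Assumed group ICC | DE | True error of a naive 5% test | Power, 878 per arm | Power, 1175 per arm | n per arm for 80% |
|---|---|---|---|---|---|
| 0 | 1.000 | 5.0% | 80.0% | 90.0% | 878 |
| 0.02 | 1.110 | 5.6% | 77.9% | 88.5% | 926 |
| 0.05 | 1.275 | 6.6% | 74.8% | 86.1% | 997 |
| 0.10 | 1.550 | 8.3% | 70.0% | 82.0% | 1115 |

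At 1175 per arm, power falls below 80% only at a group ICC of about 0.126 (6.5 per group) or 0.087 (9 per group).

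**Step 5: secondary power at 878 per arm.** Replacing 2/878 by (1 + DE)/878, at ICC 0.05 PSS has 90.6% and SPSQ 97.6%; at ICC 0.10 they have 87.1% and 96.0%. PAM equals SPSQ, because 4/20 = 0.1/0.5.

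**Step 6: facilitator level, illustration only.** The protocol gives neither the number of midwives nor an ICC. Assuming ICC 0.01 and 878 women spread evenly, 30 midwives give a true error of 6.7% and power of 75%; 12 midwives give 9.3% and 67%. At 1175 per arm, 30 midwives give 84.5% power, and 12 give 76.0% with an error of 10.8%. With a fixed number of midwives, recruiting more women raises the error, because each midwife then teaches more of them.

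**The case against.** **The primary analysis.** A reader might infer that clustering is left out of every test. The protocol does not show that. The primary outcome is assigned a mixed model, which can carry a group or facilitator effect, and the random-effect structure may be set out in a statistical analysis plan. That stands: for the primary outcome the structure is unspecified, not shown to be absent. The secondary outcomes differ, because the model named for them has no cluster term.

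**Power.** A reader might also infer that the trial will miss 80% power. That holds for the 878 per arm in section 7.1. It does not hold for group clustering at the Abstract's 2350, where power stays above 80% across the assumed range. If the surplus were a reserve for about 25% attrition (2350 × 0.75 = 1762.5), the shortfall would return. The protocol does not say so, and the primary outcome comes from a hospital database. Secondary power is not threatened by group clustering.

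**Source of the correlation.** Groups are formed by locality after individual randomisation. Similarity from locality produces a positive ICC but does not inflate the error; a simulation with a locality ICC of 0.05 gave a naive error of 4.9%. Inflation needs real group- or midwife-specific effects around a zero average effect. This condition belongs in the finding. The protocol's own account of how the programme works makes such effects plausible, but does not establish their size.

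**Size.** At small group ICCs the inflation is modest. The larger facilitator figures rest wholly on assumed inputs.

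**Insulation of the primary outcome.** Epidural use is an objective record, session 4 takes place after birth, and couple dependence does not apply because the outcome is the woman's. This limits the concern for the primary outcome and leaves the questionnaire outcomes untouched.

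**Conclusion.** The point stands for the secondary outcomes as written: PSS, SPSQ and PAM are tested without a cluster term although the protocol itself identifies the dependence. For the primary outcome it stands as an unspecified random-effect structure.

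If shared group effects exist, the true error of a nominal 5% test is about 5.6% to 8.3% for assumed group ICCs of 0.02 to 0.10 and groups of 6.5. A larger trial does not reduce it. The 878 per arm then carries 78% to 70% power instead of 80%, and 1175 per arm would carry 88% to 82%. Which pair applies cannot be settled, because 1756 and 2350 are not reconciled. Facilitator effects could matter more than group effects, but the protocol gives nothing from which to size them.

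**What to change.** In section 7.2:

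- Name a partially nested random effect for education group in the intervention arm, with control women as singletons, in the primary logistic mixed model and in linear mixed models for PSS, SPSQ and PAM. Add a facilitator effect if the number of midwives allows it.
- Define clusters by the group to which a woman was meant to be invited, so that non-attenders stay in the intention-to-treat comparison.
- State whether the tests use women only. If partners' data enter a test, include a couple effect.
- If facilitators are few, use a small-sample correction. Plain cluster-robust standard errors are anti-conservative with few clusters.

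In section 7.1, state an assumed ICC and group size, give power at both 1756 and 2350 women, and explain how the two numbers relate.

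The cost is analysis wording and code, since the planned ICCs already need group and facilitator identifiers. Intervals become slightly wider and the stated power less favourable. A random effect in one arm would also reveal which of X and Y is the intervention, so the data manager should run pre-written code until the blinded conclusions of section 3.4 have been drawn.
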